## Abstract

**Background:**

Major depressive disorder (MDD) is one of the most common mental disorders in adolescence carrying a serious risk of adverse development later in life. Extant treatments are limited in effectiveness and have high drop-out and relapse rates. A body of literature has been published on the association between distressing/ traumatic experiences and development and maintenance of MDD, but the effectiveness of a trauma-focused treatment approach for MDD has hardly been studied. This study aims to determine the effectiveness of eye movement desensitization and reprocessing (EMDR) therapy as stand-alone intervention in adolescents diagnosed with MDD.

**Methods:**

This study will be a randomized controlled trial with two conditions: (1) EMDR treatment (6 sessions) and (2) waiting list condition (WL: 6 weeks, followed by EMDR treatment). First, participants receive a baseline measure after which they will be randomized. Participants will be assessed post-intervention after which the WL participants will also receive six EMDR sessions. Follow-up assessments will be conducted at 3 and 6 months follow-up. Study population: In total, 64 adolescents (aged 12–18) diagnosed with a major depressive disorder (DSM-5) and identified memories of at least one distressing or traumatic event related to the depressive symptomatology will be included. Main study parameters/endpoints: Primary outcome variables will be the percentage of patients meeting criteria for MDD classification, and level of depressive symptoms. Secondary outcome measures include symptoms of PTSD, anxiety, and general social-emotional problems. At baseline, family functioning and having experienced emotional abuse or neglect will be assessed to explore whether these factors predict post-treatment outcome.

**Discussion:**

With the present study, we aim to investigate whether EMDR as a trauma-focussed brief intervention may be effective for adolescents with a primary diagnosis of MDD. EMDR has been proven an effective treatment for traumatic memories in other disorders. It is hypothesized that traumatic memories play a role in the onset and maintenance of depressive disorders. Particularly in adolescence, early treatment of these traumatic memories is warranted to prevent a more chronic or recurrent course of the disorder.

**Trial registration:**

International Clinical Trial Registry Platform (ICTRP): NL9008 (30–10-2020).

## Administrative information

**Table Taba:** 

Title {1}	Effectiveness of Eye Movement Desensitisation and Reprocessing (EMDR) for Adolescents with Major Depressive Disorder
Trial registration {2a and 2b}	International Clinical Trial Registry Platform (ICTRP) Registered on October 30, 2020 https://trialsearch.who.int/Trial2.aspx?TrialID=NL9008 Title Effectiveness of EMDR for adolescents with Major Depressive Disorder Scientific title Effectiveness of EMDR for adolescents with Major Depressive Disorder Study type Interventional Control group Waiting list Grouping Parallel Arms 2 or more arms, randomized Masking Single Target size 64 Inclusion criteria (a) age 12–18 years (b) Major Depressive Disorder (MDD) as primary classification (DSM-5) (c) identified memories of at least one distressing or traumatic event related to the depressive symptomatology Exclusion criteria (a) psychotic symptoms that require immediate treatment (b) suicidal attempt or serious non-suicidal self-injury requiring hospitalization in the past month (c) substance dependence (d) IQ estimated to be ≤ 80 based on information from the referral letter or diagnostic phase (e) insufficient Dutch language skills Start date 2020–11-02 Stop date 2023–04-30 Diseases Major Depressive Disorder Interventions Participants in the EMDR intervention group receive EMDR treatment during six weeks (six sessions). Participants in the waiting list condition receive EMDR treatment during six weeks after a waiting time of six weeks Primary outcome Main parameter will be the effect of EMDR treatment on depressive symptomatology. Depressive symptoms will be measured by the CDI-2 and K-SADS-PL-5 Secondary outcome Secondary parameters focus on the effect of EMDR treatment on comorbid PTSD, anxiety and overall social-emotional problems, measured by CATS, SCARED and SDQ. We will examine whether baseline posttraumatic stress symptoms severity, family functioning (measured by the FAD) and having experienced emotional abuse or neglect (CTQ) significantly predicts post-treatment outcome MEC approved Yes Multicenter Yes Randomized Yes Issueing body Medisch-ethische toetsingscommissie Leiden Den Haag Delft, the Netherlands Source ID NL77425.058.20 Funding sources Vereniging EMDR Nederland; EMDR Europe Association Old NTR ID N/A Date registered 2020–10-30
Protocol version {3}	October 3 2022 Version 2
Funding {4}	The present study is supported by grants from Vereniging EMDR Nederland and EMDR Europe Association

## Introduction

### Background and rationale {6a}

Major depressive disorder (MDD) is one of the most common psychiatric disorders of adolescence [1]. It is estimated that 14 to 25% of adolescents experience at least one episode of a depressive disorder before reaching adulthood [2]. MDD is a debilitating disease, often resulting in impairment in functioning on multiple life domains [3, 4]. Furthermore, multiple studies associated MDD with adolescent onset with other mental health disorders, elevated suicidal risk and physical complaints later in adult life [4, 5] as well as with social and legal problems [6]. Current treatments show limited effectiveness and high drop-out and relapse rates. Cognitive behavioural therapy (CBT) is the recommended treatment for MDD in adolescents [7]. A meta-analysis [8] only showed a small effect sizes for psychological treatment of MDD (i.e. Cohen’s *d* = 0.29). These findings suggest that it is of paramount importance to develop innovative strategies for treatment of adolescent MDD.

It has long been recognized that distressing and traumatic experiences relate to the development and maintenance of MDD [9, 10]. More specifically, it was found that traumatic interpersonal experiences (such as humiliation and entrapment) [11], and different forms of childhood abuse, primarily emotional abuse and emotional neglect [10, 12], are related to MDD. Moreover, having a history of childhood trauma predicts poor efficacy of treatment [13–15]. This highlights the importance of identifying trauma histories and possibly adding trauma-focused interventions in treating depressed adolescents [14]. In addition, a developing body of research highlights the role of family relationships and interactions as being particularly relevant to the onset and maintenance of MDD in adolescents [16–18]. Family functioning predicts onset of adolescent MDD [19] and is rated as more dysfunctional in families with a depressed adolescent [20] compared to families without mental disorders. Furthermore, family dysfunctioning negatively affects treatment outcome [16, 21].

According to the recent treatment guidelines, EMDR therapy is one of the recommended treatments for post-traumatic stress disorder (PTSD) [22, 23]. EMDR therapy has proved effective in processing memories of distressing events [24]. Preliminary evidence for the efficacy of EMDR therapy in the treatment of MDD in adults has been demonstrated in multiple case studies [25, 26] and randomized controlled trials. Studies investigating EMDR therapy as an adjacent therapy to CBT [27], to pharmacological treatment [28, 29] and to inpatient treatment [30, 31] obtained promising results. As a stand-alone treatment, EMDR was proven effective in reducing depressive symptoms [32], even for patients with long-term [33] or treatment-resistant depressive disorder [29]. Moreover, significant decreases of trauma [32] and anxiety symptoms [29] were obtained with EMDR treatment of MDD, as well as increases of social functioning [29] and quality of life [32].

Findings from a recent meta-analysis [34] suggest that EMDR can be an effective treatment for depression. Moreover, studies using EMDR showed not only a large effect, but results of EMDR treatment were superior to non-trauma-focused CBT. However, these studies included adult patients only. Our group conducted one of the first studies investigating the effectiveness EMDR therapy in a group of 32 adolescents with a primary diagnosis of MDD [35]. After six EMDR sessions, 60.9% of the adolescents who finished treatment no longer met DSM-IV criteria of MDD. In addition, comorbid anxiety, post-traumatic stress symptoms and somatic complaints were significantly reduced. At three-month follow-up, these results were maintained. Since this pilot study only included a small sample size and no control group, higher-quality studies are needed to explore these promising results.

### Objectives {7}

Building on the study by [name] et al. [35], the current study aims to investigate whether EMDR therapy is more effective in comparison to a waiting list control condition.

#### Hypothesis 1

EMDR therapy is associated with a significant decrease in severity of depressive symptoms and decrease in percentage of patients meeting DSM-5 criteria for MDD compared to the waiting list.

Outcome measures: Total score on the CDI-2 and the percentage of patients meeting DSM-5 criteria for MDD (K-SADS-PL-5).

#### Hypothesis 2

After treatment with EMDR, participants report less comorbid PTSD, anxiety and social/emotional symptomatology in comparison to those in the waiting list control condition.

Outcome measures: severity of PTSD (CATS), anxiety (SCARED) and social/emotional symptoms (SDQ).

The second aim of this study is to investigate predictors of treatment outcome. We will test the following predictors: baseline PTSD symptoms (CATS), family functioning (FAD) and experienced emotional abuse or emotional neglect in childhood (CTQ).

#### Hypothesis 3

A higher level of post-traumatic stress symptoms at baseline predicts a stronger post-treatment reduction in depressive symptoms.

Outcome measures: reduction of depressive symptoms (CDI-2 total score), severity of post-traumatic stress symptoms (CATS total score).

#### Hypothesis 4

A higher level of family dysfunction at baseline predicts smaller post-treatment reductions of depressive symptomatology.

Outcome measures: severity of depressive symptoms (CDI-2 total score), family functioning (FAD, general functioning score and dimension scores).

#### Hypothesis 5

A higher level of emotional abuse or neglect at baseline predicts smaller post-treatment reductions of depressive symptomatology.

Outcome measures: reduction of depressive symptoms (CDI-2 total score), experience of emotional abuse or neglect (respective subscales CTQ).

### Trial design {8}

This study is designed as a randomized, controlled, single-blinded two-center superiority trial with two parallel groups. All patients meeting the inclusion criteria are asked for written informed consent to participate in the intervention study. For consenting participants, baseline measures (T0) are completed subsequently. Randomization will be performed as block randomization with a 1:1 allocation stratified per treatment location. An independent researcher will conduct randomized allocation by using the SPSS function to produce random numbers. Hence, the main researcher will be blind to the randomization process. Randomization will take place in blocks of 10 participants. After completing the baseline assessments (T0), participants will be informed in which group they have been randomized. Assessments (see Fig. 1) are scheduled pre-treatment (T0), post-treatment (T1), and at 3-month (T2) and at 6-month (T3) follow-up. Assessment will be done by a team of independent assessors (i.e. trained clinicians and supervised master level students) who are blind for condition. Participants in the waiting list condition are offered EMDR treatment after T1 and are subsequently assessed post-treatment and at 3 and 6 months follow-up (see Fig. 1). For participants in the waiting list condition, T1 will be labelled as T0WL when they enter treatment (*t*_*1*_ = *t*_*0-wl*_).

**Fig. 1 Fig1:**
[figure not shown]
Participant timeline. *Recommended content can be displayed using various schematic formats. See SPIRIT 2013 Explanation and Elaboration for examples from protocols. **List specific time points in this row

## Methods: participants, interventions and outcomes

### Study setting {9}

Participants will be recruited from outpatient clinics of GGZ Rivierduinen Department Youth (locations Leiden, Katwijk, Leidschendam and Zoetermeer) and GGZ Delfland (locations: Bergschenhoek, Delft, Naaldwijk, Nootdorp en Schiedam), two institutions for mental health care in the Netherlands.

### Eligibility criteria {10}

Inclusion criteria for participants:Age 12–18 yearsMajor depressive disorder (MDD) as primary diagnosis (DSM-5)Identified memories of at least one distressing or traumatic event related to the depressive symptomatology

Exclusion criteria for participants:Psychotic symptoms that require immediate treatmentSuicidal attempt or serious non-suicidal self-injury requiring hospitalization in the past monthSubstance dependenceIQ estimated to be ≤ 80 based on information from the referral letter or diagnostic phaseInsufficient Dutch language skills

### Who will take informed consent? {26a}

Prior to the study, potential participants and their parents will be approached by the researcher or the research assistant and receive oral and written information about the content, purpose and research design. If all parties agree, informed consent will be signed by both participants and their parents.

### Additional consent provisions for collection and use of participant data and biological specimens {26b}

On the consent form, participants will be asked if they agree to use of their data should they choose to withdraw from the trial. Participants will also be asked for permission for the research team to share relevant data with people from the Universities taking part in the research or from regulatory authorities, where relevant. This trial does not involve collecting biological specimens for storage.

## Interventions

### Explanation for the choice of comparators {6b}

Effectiveness of EMDR is compared to an inactive condition (waiting list). To our knowledge, this is the first study investigating the effectiveness of EMDR therapy on the reduction of adolescent depressive symptoms. The waiting list control group serves two purposes. First, it provides an untreated comparison for the EMDR group to determine if EMDR therapy is effective in this specific group. Second, it allows the wait-listed participants the opportunity to obtain the EMDR intervention after 6 weeks.

### Intervention description {11a}

Prior to participation, a patient safety plan will be made with each participant; this is part of the standard screening and assessment routine of the participating organizations.

#### EMDR therapy

The Dutch version of the standard EMDR protocol with age-specific adaptations for children and adolescents [36] will be used. This procedure includes eight phases: history taking, preparation, assessment, desensitization, installation, body scan, closure and re-evaluation. Before start of the treatment, a case conceptualization is made to guide the sessions. Memories are placed in a hierarchy based on the subjective units of disturbance (SUD), and will be treated subsequently from high to low SUD. If all depression-related target memories from the case conceptualization can be retrieved without emotional disturbance (i.e. SUD related to the memory is reduced to zero) in less than six sessions, a participant will be classified as an early completer.

Treatment consists of a maximum of six weekly 60-min individual treatment sessions. Each session will be followed by a 15-min meeting with the therapist, adolescent and one or both parents. The content of this meeting is discussed beforehand with the adolescent and comprises any one of the following elements: (1) a content outline of the session, (2) parents’ view on the course of symptoms in the week before the session and (3) the need and possibilities for emotional support of the adolescent after the session. During EMDR treatment, the number of adverse events such as symptoms exacerbation, crisis contacts and self-injurious or suicidal behaviour, will be recorded each session.

#### Waiting list

For participants in the waiting list condition, a therapist is available in case of crisis or sudden worsening of symptoms; a record will be made of such contacts.

### Criteria for discontinuing or modifying allocated interventions {11b}

Participants can leave the study at any time for any reason without any consequences. The investigator can decide to withdraw a participant from the study for urgent medical reasons.

### Strategies to improve adherence to interventions {11c}

For each participating location, 1–2 EMDR therapists will be recruited from the local staff. Therapists have at least completed the official Basic and Advanced EMDR training (approved by EMDR European Association (EMDREA). Group supervisions will be given monthly by a certified EMDR Europe Child and Adolescent Consultant (CdR). All EMDR sessions will be videotaped and all therapists participate in monthly 2-h supervisions by a certified EMDR Europe Child and Adolescent Consultant (CdR). Therapists will report their EMDR sessions through session reports that are shared with the consultant after each session. Upon request, additional supervision is provided via email and telephone.

### Relevant concomitant care permitted or prohibited during the trial {11d}

During participation, no concomitant care or interventions are permitted, except for stable doses of medication already prescribed before participation.

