### Provisions for post-trial care {30}

After completing the EMDR intervention, the therapist evaluates the effects of treatment with the participant, his/her parents and the responsible practitioner. The therapist also consults the multidisciplinary staff to jointly decide if further treatment is indicated, and if so further treatment will be offered.

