## Discussion

The present study is the first single-blinded randomized controlled trial with a 6-month follow-up period that investigates the effectiveness of EMDR therapy on depressive and comorbid symptoms in a sample of adolescents. We expect that EMDR therapy is associated with a significant reduction in depressive and comorbid symptoms. We consider this of great importance, given the limited effectiveness of current psychotherapies for adolescent MDD [8, 56].

The current study has several strengths. Firstly, it is a multicentre outpatient trial with a variety of MDD patients and a large number of EMDR therapists, enhancing the external validity of the study. Secondly, thorough assessment of psychopathology is offered using a standardized DSM-5-based clinical interview, by assessors blind to treatment condition. Thirdly, a shorter treatment length, compared to current NICE guidelines [4]. Fourthly, the study includes two follow-up measurements, documenting the longevity of the hypothesized effects. Fifthly, treatment protocol adherence by EMDR therapists will be evaluated utilizing video recordings. This may help therapists to stay focused and stick to the protocol. Eventually, it will be possible to determine to what extent the protocol was applied correctly.

With the present study, we aim to investigate whether EMDR as a trauma-focused brief intervention may be effective for adolescents with a primary diagnosis of MDD. It is hypothesized that traumatic memories play a role in the onset and maintenance of depressive disorders. Especially in adolescence, early treatment of these traumatic memories is warranted to prevent a more chronic or recurrent course of the disorder. For adults, there is some evidence that EMDR is effective in treating traumatic memories in MDD [34]. It is expected that EMDR will decrease depressive symptoms as well as comorbid post-traumatic stress, anxiety, somatic complaints and overall social emotional functioning in adolescent patients with a primary diagnosis of a depressive disorder who also experienced at least one distressing or traumatic event related to the depressive symptomatology.

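### The 3- and 6-month follow-ups cannot document how long the EMDR effect lasts: no untreated arm remains, and further treatment may start before them

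*Protocol article*

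**What the plan says.** Five parts of the protocol article bear on this point.

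- **Concomitant care {11d}**, whose heading refers to the trial as a whole: "During participation, no concomitant care or interventions are permitted, except for stable doses of medication already prescribed before participation".
- **Post-trial care {30}**: "After completing the EMDR intervention, the therapist evaluates the effects of treatment with the participant", the parents and the responsible practitioner. The therapist then consults the multidisciplinary staff "to jointly decide if further treatment is indicated, and if so further treatment will be offered". No limit is placed on the type or start date of that treatment.
- **Trial design {8}**: "Assessments (see Fig. 1) are scheduled pre-treatment (T0), post-treatment (T1), and at 3-month (T2) and at 6-month (T3) follow-up". It adds: "Participants in the waiting list condition are offered EMDR treatment after T1".
- **Retention {18b}**: T1 belongs to the routine evaluation of treatment, and its results go to the EMDR therapist for use in that evaluation.
- **Discussion**: among the trial's strengths, "the study includes two follow-up measurements, documenting the longevity of the hypothesized effects".

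The statistical methods section {20a} plans Cohen's d for the change from baseline to T1 and from baseline to T2 and T3.

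**The concern.** Durability of an EMDR effect can be read from T2 and T3 only if what happens between T1 and T3 can be attributed to EMDR. Two features of the plan prevent this.

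First, no untreated group is left after the waiting list has moved to EMDR, so natural recovery cannot be separated from a lasting treatment effect.

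Second, further treatment can be offered from T1 onward. It would not be spread at random. It is offered where indicated, in a decision in which the therapist takes part with the T1 results in hand, so participants with residual depression are the likeliest to receive it. Any later gain in that group would make the baseline-to-follow-up effect sizes look maintained or larger.

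A reader could then take a sustained six-month effect as a property of six sessions of EMDR given as a stand-alone treatment, which is how the Abstract frames the aim. The data as planned could not distinguish that from EMDR plus later care plus time.

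**Working it through.** The plan gives no figure for this point, so the check sets the sections side by side and counts out the timeline.

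**Step 1: who is untreated at follow-up?** Inputs: 64 randomised 1:1, so 64 / 2 = 32 on the waiting list (Sample size {14}); 6 weeks of waiting, then 6 weeks of EMDR (Abstract).

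- T1 falls at about week 6.
- Waiting-list EMDR ends at about week 6 + 6 = 12.
- The 3-month follow-up of the EMDR arm falls at about week 13 if counted from baseline, or about week 6 + 13 = 19 if counted from T1.
- Both are later than week 12. By schedule, 0 of 32 controls are still untreated at T2, and 0 of 32 at T3.

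**Step 2: when can further treatment start?** The decision in {30} is triggered by completing EMDR. Section {18b} ties the treatment evaluation to T1. The whole interval from T1 to T3 is therefore exposed.

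**Step 3: does {11d} close that interval?** This depends on when participation ends, which is not defined.

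| Reading | Relation of {11d} to {30} | What T2 and T3 measure |
|---|---|---|
| Participation ends at T3 | They conflict: other care is barred in a period in which it is also offered | Unclear, because the two rules give different answers |
| Participation ends with EMDR, at T1 | No conflict | EMDR plus any later treatment |

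The protocol's own usage leans to the first reading. The heading of {11d} speaks of the trial. Section {14} counts drop-out over treatment and follow-up together. Section {18b} gives the voucher after the last measurement and asks those who stop treatment to continue with measurements. The Discussion describes a trial with a 6-month follow-up. None of this is a definition.

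**Step 4: what do the planned estimates show?** The T0–T2 and T0–T3 effect sizes divide a mean change from baseline by a pooled standard deviation. With no concurrent untreated arm, each is a within-group change. It combines the EMDR effect, natural course and any further treatment, and the plan gives no means of separating them.

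**Step 5: how many might be affected?** The documents do not say. As illustration only: in the group's pilot, 60.9% of those who finished treatment no longer met MDD criteria, so 100% − 60.9% = 39.1% still did. If half of these went on to further treatment, that would be 39.1% / 2 = 19.6% of finishers; if all did, 39.1%. These are not bounds. The pilot figure covers finishers only and uses DSM-IV criteria, the shares of one half and all are assumptions, participants in remission may be offered care for other problems, and those not in remission may decline it. Receiving further treatment also does not show that it changed the outcome.

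**The case against.** The strongest reply has four parts.

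**The sections need not clash.** Section {11d} concerns care given alongside the allocated condition, and {30} is headed as post-trial care. Read so, one covers the treatment or waiting phase and the other what follows. This stands in part: a reader might infer a flat contradiction, but that requires participation to run to T3, which the protocol suggests and never states. The reply does not rescue the longevity claim, since on this reading co-treatment during follow-up is allowed.

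**The crossover is declared and explained.** This stands. A reader might infer that the missing control arm at T2 and T3 is a design error. It is an open choice with a stated reason (Explanation for the choice of comparators {6b}). The fault lies in what the follow-up data are said to show.

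**No hypothesis rests on T2 or T3.** This also stands. Hypotheses 1 and 2 compare EMDR with the waiting list, Hypotheses 3 to 5 concern post-treatment reductions, and the chi-square test is set at T1. The longevity claim is one clause in a list of strengths. It is nonetheless the only interpretation the protocol gives to two of its four assessments.

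**The handling of later treatment belongs in the analysis plan.** This is fair for the detail, and its absence here is not held against the protocol. What is raised is in the text shown: two care sections with no defined boundary, and a claim that the design cannot deliver. An intention-to-treat course that includes later care is a legitimate description of follow-up, provided it is labelled as such.

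**Conclusion.** The point holds in a limited form. Sections {11d} and {30} conflict if participation runs to T3, and leave follow-up open to selective co-treatment if it ends at T1. On either reading the T2 and T3 effect sizes are uncontrolled within-group changes, so the statement that the follow-ups are "documenting the longevity of the hypothesized effects" is not supported.

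The conclusion rests on the stated crossover, on a decision about further care made at EMDR completion, and on T1 results informing the evaluation that leads to it. It does not depend on how many participants receive further treatment. That number is unknown, and the 20% to 39% illustration should not be quoted as a range for this trial.

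A reader might infer that the trial's main result is compromised. The documents do not support that: this point leaves the randomised EMDR versus waiting-list comparison at T1 unaffected. The matter should be corrected because it changes what may be concluded about durability.

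**What to change.** 1. State when participation ends and reconcile {11d} with {30} accordingly. Which care rule applies is for the investigators; this review does not choose one.
2. Record the type and start date of any treatment begun between T1 and T3, at the existing follow-up contacts.
3. Report T2 and T3 as uncontrolled within-group course, alongside the proportion who received further treatment before each assessment.
4. Add one sensitivity analysis using a single stated strategy for CDI-2 and MDD status alike, for example results with and without assessments made after further treatment began. Leaving those assessments out tends to remove participants who did worst at T1, so the result is a check on robustness and does not isolate the EMDR effect.
5. Reword the Discussion so that the follow-ups describe the course of symptoms over six months after EMDR, including any later care.

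The cost is a few extra questions at contacts already planned, one additional analysis and a softer claim. Sample size, randomisation and the T1 analysis stay as they are.
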